### Secondary outcomes

Health-related quality of life will be assessed by the Brazilian version of the Medical Outcomes Study Short Form Questionnaire – SF-36 [31].

### Procedures

First, eligible older women will be informed of the study’s objectives and procedures of datacollection methods. The benefits and risks involved in voluntary participation will be stated. A researcher will provide this information in an interview, using an information sheet. If the volunteer decides to participate in the study, a written consent statement will be obtained.

The Mini-Mental State Examination will then be applied to assure cognitive capacity for participation in the study. Volunteers with a score <17 will not be included in the study [32].

A clinical questionnaire was prepared to collect sociodemographic, anthropometric and clinical data to characterise the study sample. Participants will be classified as frail, prefrail or nonfrail according to the criteria proposed by Fried and colleagues [30]. The Brazilian version of the Human Activity Profile will be applied to characterise participants into three categories: inactive, moderately active and active [33]. The Geriatric Depression Scale short form – GDS-10 [34] will be used to assess possible depressive symptoms in the volunteers.

After an initial interview, each participant will undergo the functional tests in a random order. In each test, the presence of pain in the lower limbs and the rate of perceived exertion [35] will be registered. The Brazilian version of the Short Physical Performance Battery will be used for tests of balance, walking speed and rising from a chair [36]. The best time of two trials in each of these tasks will recorded, and participant performance will be classified on a 4-point scale for each test [37].

The shuttle walking test will be conducted to calculate maximum walking speed [38]. In this test, the volunteer must walk a 10-metre course at progressively higher speeds, trying to make this distance before a beep sounds. During the test, the beeps will become closer every minute, leading the volunteer to walk at an ever-increasing rate. The initial velocity is 0.5 m/second, which increases by 0.17 m/second every minute, for a maximum duration of 12 minutes. The test is stopped when the individual cannot reach the end of the course before the beep in two successive trials.

Locomotion on stairs will be tested on a flight of 10 stairs with a handrail. In the first test, volunteers will be instructed to climb the stairs in their usual way, going up and down at once. The second test is to climb the flight of stairs as quickly as possible, stopping at the top of the stairs. Each test is performed twice, and the best time is recorded to calculate the usual stair speed and maximum stair speed as the ratio between the height of the stairs and the time spent to accomplish the task [39].

To prevent potential fatigue, muscle performance tests will be conducted on a day after the interview and functional tests. For tests of knee flexors and extensors, the manufacturer’s protocols (Biodex System 3 Pro; Biodex Medical Systems Inc.) will be followed in the sitting position. For hip muscles (flexors/extensors and the abductor/adductor groups), the tests will be performed in a standing upright position, using a stabilising device specially built for this purpose [40]. The testing order of muscles will be randomised by drawing lots. For each muscle, two different tests will be conducted. First, a test of five maximum concentric repetitions at an angular speed of 60°/second will be conducted to calculate strength as the total work (Joules) and peak torque (Newton-meters). Next, a test of 15 repetitions at a speed of 180°/second for knee muscles and 120°/second for hip muscles will be performed to calculate power as the work done per unit time, expressed in Watts [41]. All measures will be normalised to body weight.

Data collectors will be blinded to the participants’ later randomisation into groups.

### Randomisation

After complete baseline assessment, a randomisation sequence will be created using a computer-generated list of random numbers in block sizes of three. The allocation sequence will be concealed from the researchers enrolling and assessing participants, since it will be performed by an external researcher. The allocation of each participant will then be communicated to the researchers involved in the exercise programmes and to those responsible for monitoring the control group.

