**Methods/Design:**

This is a protocol study for a parallel randomised controlled clinical trial. Eligible participants are older women (≥65 years) with a body mass index ≥30 kg/m ^2^ and hand grip strength ≤21 kg force. A total sample of 36 participants will be randomly allocated to one of the intervention groups in blocks of three: land-based, aquatic or control. Each intervention group will undergo 2-week sessions of a 10-week therapeutic exercise programme for strength, power and endurance training of the lower-limb muscles. Participants in the control group will not participate in any strengthening activity for lower limbs and will receive telephone calls once a week. Baseline and final evaluation of outcomes will encompass muscle performance of the lower limbs assessed by an isokinetic dynamometer; functional tests of usual walking speed, maximal walking speed (shuttle walking test), stair speed and the Short Physical Performance Battery; and health-related quality of life (Medical Outcomes Study Short Form Questionnaire – SF-36). Data collectors will be blinded to randomisation and will not be in touch with participants during the interventions.

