### Sample size

The effect size of the interventions was estimated at *f* = 0.20, based on previous studies of similar exercise programmes and the target population [15,26,27] and a pilot study conducted with 12 volunteers. The sample size was calculated assuming a mixed design of repeated-measures analysis of variance in the programme G* Power, version 3.1.2 [28], considering α = 0.05, β = 0.80, three groups and a correlation of 0.8 between the two repeated measures, with a resultant total of 30. Adding a possibility of 15% missing participants, the final sample size was calculated as 36, with 12 subjects per group. Figure 1 shows the flow diagram for participants in this study.

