### Interventions

Each intervention group will undergo a therapeutic exercise programme designed to improve the strength, power and endurance of lower-limb muscles. Independent researchers who did not participate in the data collection will conduct the exercise sessions.

The exercise sessions will be done in groups of six volunteers, accompanied by at least two researchers. Each programme will last 10 weeks, with 1-hour sessions twice a week. Frequency of attendance and adverse clinical events that occur during the sessions will be registered on a daily record sheet.

The exercise programmes were designed to follow recommended principles of prescription and progression of resistance training for older adults in general and in the aquatic environment [13,42]. Researchers conducting the training sessions will guide the exercise execution with abdominal contraction, spine stabilisation and correction of lower-limb alignment and upright stance. The guidance will include verbal, tactile and visual information to ensure the correct muscle contraction demanded by the exercises.

Each session will comprise a 5-minute walk for warm-up and lower-limb exercises for stretching and strengthening, with a resting time of 30 seconds between sets and 1 minute between exercises. Stretching exercises will comprise posterior, anterior, lateral and medial lower-limb muscles, performed for 60 seconds in each leg. Strengthening exercises will be performed in open and closed chains of lower limbs.

In the first 4 weeks of the intervention, both land-based and aquatic programmes will emphasise resistance exercises for strengthening muscles, with concentric and eccentric movements performed at a low speed. Beginning in the fifth week of training, participants will be instructed to add increasing speed to each exercise, focusing on muscle power.

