## Discussion

To the best of our knowledge, this is the first randomised controlled trial designed to evaluate the benefit of resistance exercises for older people with sarcopenic obesity. Considering the obesity epidemic and sedentary habits of western populations in general, it is essential to find interventions that can address both problems. We chose to select only older women because of their greater longevity and higher risk of functional disabilities.

Providing assurance that rehabilitation techniques are really effective in an evidence-based way is important. To achieve this, we developed a study design using an appropriate power calculation to estimate the sample size. This clinical trial will provide substantial information about the effects of a common practice in the rehabilitation field. Exercise interventions are considered a nonpharmacologic and noninvasive technique that can improve functional capacity and prevent or reverse disabilities. If our hypothesis is correct, both intervention programmes will be effective, and the land-based intervention will produce better results for muscle performance and functional capacity. We will also investigate the effects on health-related quality of life.

Following the CONSORT Statement recommendations for randomised trials of nonpharmacologic treatments, we described our intervention protocols in detail, including all qualitative and quantitative components. Training and constant supervision will guarantee the programmes’ standardisation. In the interventions proposed in this protocol, it is not possible to blind participants or those administering the interventions. Researchers involved in outcomes assessment will thus be blinded to participant allocation and will have no contact with participants besides evaluation tests. Any harm or adverse events will be recorded and reported. Important to note is that it is completely feasible to carry out the exercise programmes proposed in this study in clinical settings. Our results will be analysed and published after discharge of the last randomised patient.

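### A single block size of three, equal to the number of arms, makes concealment fragile if allocations leak: two known allocations in a block fix the third

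*Protocol article*

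**What the plan says.** The Randomisation section creates the sequence after baseline assessment from a "computer-generated list of random numbers in block sizes of three". No other size is given and sizes are not said to vary. The abstract discloses the same rule: participants are "randomly allocated to one of the intervention groups in blocks of three". The Sample size section sets equal arms: "the final sample size was calculated as 36, with 12 subjects per group".

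On blinding, the Discussion states that "it is not possible to blind participants or those administering the interventions". Outcome assessors are to be blinded and to meet participants only at the evaluation tests.

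The stated safeguards are these:

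- Randomisation section: "The allocation sequence will be concealed from the researchers enrolling and assessing participants, since it will be performed by an external researcher".
- Same section: each allocation is then "communicated to the researchers involved in the exercise programmes and to those responsible for monitoring the control group". No other recipient is named.
- Interventions section: those who run the exercise sessions take no part in data collection.

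**The concern.** With three arms and equal allocation, three is the smallest possible block, so the sequence is as predictable as permuted blocks allow. Every participant knows her own arm, and the exercise staff and control-group monitors know the allocations. Keeping the list with an external researcher protects the list. It does not stop someone inferring the next entry from those already made.

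Two things would be at stake if allocations leaked.

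- **Selection at entry.** Women are invited by telephone from a known database, and some exclusions call for judgement, such as inability to adapt to water. With 12 women per arm, one steered entry is 1/12 = 8% of an arm.
- **Outcome assessment.** Dynamometry and walking tests depend on effort and encouragement. An assessor who learns two allocations in a block could infer a third woman's arm before her final test.

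**Working it through.** **Inputs.** Three arms and blocks of three (Abstract; Randomisation); N = 36, 12 per arm (Sample size). The article states no predictability figure to reproduce. Its sample size does reproduce: for the group-by-time interaction with f = 0.20, correlation 0.8 and α = 0.05, power is 0.794 at N = 27 and 0.843 at N = 30, and 30/(1 − 0.15) = 35.3, which rounds up to 36 in three equal arms. Block size does not enter that calculation.

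**Fixed blocks of three.** Each block holds each arm once, and there are 36/3 = 12 blocks. For someone who knows all earlier allocations in order, the best guess is right with probability:

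- first place: 1/3
- second place: 1/2 (one arm excluded)
- third place: 1 (two arms excluded)

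Allocations that are certain: 12 × 1 = 12 of 36 = 33.3%. A further 12 are 50:50.

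Expected correct guesses: (1/3 + 1/2 + 1)/3 = 0.611, or 22 of 36.

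These are upper bounds, because they assume every earlier allocation and its order is known.

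**Alternatives.** These were simulated for N = 36. The guesser updates by Bayes' rule and knows all earlier allocations and the list of possible sizes, but not the order in which varying sizes occur.

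| Blocking | Certain | Correct guesses |
|---|---|---|
| Fixed 3 | 33.3% | 61.1% |
| Fixed 6, size known | about 20% | about 56% |
| Fixed 9, size known | about 14% | about 53% |
| Random 3, 6, 9 | about 3–4% | about 55% |

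Under random 3, 6, 9, about 0.035 × 36 ≈ 1.3 allocations are certain instead of 12, and about 0.55 × 36 ≈ 20 guesses are right instead of 22. If the sequence is constrained to end exactly at 36, the results are much the same (3.8% and 56%). Most of the gain is therefore in removing certainty; the average guess improves by only about 6 percentage points.

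**Batch release.** If no allocation in an intake is disclosed until everyone in it has completed baseline, and intakes are whole blocks, earlier allocations say nothing about the next woman at the time she is enrolled. The predictive gain at entry is zero.

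**The case against.** A reader might infer that concealment and assessor blinding are already undermined. The document does not support that. To make the deduction, recruiting or assessing staff must learn two allocations, know that they belong to one block, and know the randomisation order. The protocol directs allocations away from these staff, and no section gives them that information. This part of the objection stands: the weakness is conditional on a leak. The safeguards lower the chance of a leak, however; they do not limit what can be deduced after one. If women are randomised as they finish baseline, data collectors would also know the order.

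Second, the sequence is created after complete baseline assessment. If that refers to an intake or to the whole sample, enrolment is over before allocations exist and cannot be steered within that batch. Sessions run in groups of six fit this reading; entry over about two years from January 2012, with each participant's allocation then communicated, fits individual entry too. The text does not settle it.

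Third, an assessor who can infer the third arm has already lost blinding for two women, and a participant can reveal her own arm whatever the block size. This stands and makes the assessor argument the weaker one: block size extends a leak but does not create it.

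Fourth, it is tempting to set 61% against the 33% of simple randomisation. Simple randomisation is not the proposed remedy; the fair comparison is with varying blocks, at about 55%.

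Finally, the article appeared in September 2013, about 20 months into a recruitment period expected to last about 24. Publication itself may have affected few entries, and the document does not say whether recruiters knew the block size earlier.

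**Conclusion.** The point holds as an avoidable fragility, worth correcting because correction is cheap. The protocol fixes one disclosed block size equal to the number of arms, while participants and trainers know the allocations. At most 12 of 36 allocations (33%) are certain and 61% can be guessed correctly. Both figures assume full knowledge of earlier allocations and their order. The risk at enrolment further assumes that allocations are released one by one and not by intake. The effect on assessor blinding is secondary. Nothing in the document shows that any allocation was predicted or that any assessor was unblinded.

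**What to change.** For the allocations still to be made, the external researcher should draw a new list with randomly varying block sizes, for example 3, 6 and 9. The sizes should be disclosed to nobody who recruits or assesses, and block size should be removed from the documents those staff use.

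Alternatively, the Randomisation section should state that allocations are released only when a whole intake has completed baseline, or say so explicitly if this is already the practice. An intake of 18 would suit the session format: 18/3 = 6 per arm, which fills one land-based and one aquatic group of six.

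The sample size stays at 36. The first option costs a new list and, if recruitment stops mid-block, slightly unequal arms: a block of nine holds three places per arm, so the difference is at most three women, against one with blocks of three. The second costs a short wait for women enrolled early in an intake. On the stated timetable few allocations may remain, so the report should also describe the block size used, how allocations were released, and who knew them.

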### Interventions

Each intervention group will undergo a therapeutic exercise programme designed to improve the strength, power and endurance of lower-limb muscles. Independent researchers who did not participate in the data collection will conduct the exercise sessions.

The exercise sessions will be done in groups of six volunteers, accompanied by at least two researchers. Each programme will last 10 weeks, with 1-hour sessions twice a week. Frequency of attendance and adverse clinical events that occur during the sessions will be registered on a daily record sheet.

The exercise programmes were designed to follow recommended principles of prescription and progression of resistance training for older adults in general and in the aquatic environment [13,42]. Researchers conducting the training sessions will guide the exercise execution with abdominal contraction, spine stabilisation and correction of lower-limb alignment and upright stance. The guidance will include verbal, tactile and visual information to ensure the correct muscle contraction demanded by the exercises.

Each session will comprise a 5-minute walk for warm-up and lower-limb exercises for stretching and strengthening, with a resting time of 30 seconds between sets and 1 minute between exercises. Stretching exercises will comprise posterior, anterior, lateral and medial lower-limb muscles, performed for 60 seconds in each leg. Strengthening exercises will be performed in open and closed chains of lower limbs.

In the first 4 weeks of the intervention, both land-based and aquatic programmes will emphasise resistance exercises for strengthening muscles, with concentric and eccentric movements performed at a low speed. Beginning in the fifth week of training, participants will be instructed to add increasing speed to each exercise, focusing on muscle power.

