### Control group

Volunteers randomised to the control group will be instructed not to participate in physical activities that include strengthening exercises for the legs. During the 10 weeks of interventions, they will receive telephone calls once a week. In these telephone calls, a trained researcher will interrogate them about events of health problems, temporary disabilities or pain in the lower limbs, recording any clinical complications or medication use. The researcher will reinforce their obligation to maintain normal daily activities and avoid strengthening exercises. After this period, these volunteers will have the choice to participate in one of the two types of interventions in the same programme as the other groups.

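### Adverse events are captured in session in the exercise arms but by weekly questioning in controls, so exercise-versus-control harm counts would not be comparable

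*Protocol article*

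**What the plan says.** The protocol article describes harms collection in three places.

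- **Exercise arms (Interventions).** "Frequency of attendance and adverse clinical events that occur during the sessions will be registered on a daily record sheet". The exposure is fixed in the same section: "Each programme will last 10 weeks, with 1-hour sessions twice a week".
- **Control arm (Control group).** "During the 10 weeks of interventions, they will receive telephone calls once a week". In these calls, "a trained researcher will interrogate them about events of health problems, temporary disabilities or pain in the lower limbs", and clinical complications and medication use are also noted.
- **All arms (Discussion).** "Any harm or adverse events will be recorded and reported". No method, timing or source is attached to this sentence.

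Two further statements settle who could collect such data. Under Randomisation, each allocation is "communicated to the researchers involved in the exercise programmes and to those responsible for monitoring the control group", so contact during the 10 weeks lies with separate, unblinded staff. Under Discussion, the outcome assessors "will have no contact with participants besides evaluation tests".

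**The concern.** The two stated procedures differ in three ways that affect whether an event is recorded at all. They differ in window (time in session against the whole 10 weeks by recall), in method (a log kept by trainers against active questioning) and in content (temporary disability and medication use are named only for controls). Joint pain the day after training, a fall at home or a newly started painkiller falls outside the exercise-arm rule as worded. The same complaint in a control would be asked for within the week.

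What is at stake is how the reported harms will be read. The article commits to reporting them, and counts by arm are naturally set side by side. If events in the trained women are captured less completely, training may look safer against control than it is. This cannot be repaired at analysis, because an event that nobody asked about is not in the data.

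**Working it through.** **1. The stated rules side by side**

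| Feature | Land and aquatic arms | Control arm |
|---|---|---|
| Source | Session record sheet | Weekly telephone call |
| Window | During sessions | All 10 weeks, by recall |
| Content | Adverse clinical events | Health problems, temporary disability, leg pain, complications, medication use |
| Collected by | Staff running the sessions | Staff monitoring controls |

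No call or between-session enquiry is described for the exercise arms. Outcome assessors see participants only at the evaluation tests, so they do not fill the gap. The Discussion sentence states an aim but no procedure.

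**2. Is there a figure in the plan to reproduce?** There is none for harms. The only design figure is the sample size, and it does not depend on this point. For the group-by-time interaction with f = 0.20, three groups, two measures and correlation 0.8, the noncentrality is f² × N × 2 / (1 − 0.8). At N = 30 this is 0.04 × 30 × 2 / 0.2 = 12 on 2 and 27 degrees of freedom, with power 0.843. At N = 27 power is 0.794. So 30 reproduces, and 30 / 0.85 = 35.3, which rounds up to 36.

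**3. Effect of unequal capture on a recorded risk ratio.** Let s be the share of affected exercise-arm women whose event is recorded (it occurred in session), and c the share recorded in controls. Then

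recorded RR = true RR × s / c.

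The document gives neither s nor c, so both are assumed over a range. With true RR = 1:

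| s | c = 1.0 | c = 0.8 |
|---|---|---|
| 10% | 0.10 | 0.125 |
| 25% | 0.25 | 0.31 |
| 50% | 0.50 | 0.625 |

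**4. The true excess that would be recorded as no difference.** Setting recorded RR = 1 gives true RR = c / s. With c = 1.0 this is 10, 4 and 2 for s = 10%, 25% and 50%. With c = 0.8 it is 8, 3.2 and 1.6.

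**5. In participants.** Assume a 40% true 10-week risk in every arm of 12, and c = 1.0. The expected number of controls recorded is 12 × 0.40 = 4.8. Each exercise arm would record 4.8 × s = 0.48, 1.2 or 2.4.

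**6. When the direction reverses.** Recorded RR exceeds true RR only if s > c. For example, s = 1.0 with c = 0.8 gives 1.0 / 0.8 = 1.25. That needs nearly all exercise-arm events to happen in session, or trainers also to log events reported from between sessions, which the text does not provide for.

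**7. With the same questions in all arms,** s should be close to c, so s / c is close to 1 and the recorded RR approaches the true RR.

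**The case against.** The strongest reply is that there is no planned harms comparison to bias. Harms are not among the primary or secondary outcomes, and Statistical analysis plans no between-arm test of adverse events. This stands: the point concerns descriptive counts at 12 per arm.

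Second, the session sheet may be one instrument among several. The Interventions sentence does not say that nothing else is recorded, the Discussion sentence is unrestricted, and a journal article leaves detail to a fuller protocol. This stands in part. Wider capture may be intended. But the article does state a procedure for each side, and they differ, so this is not just missing detail.

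Third, the control calls also serve to discourage strengthening exercise, and the document never presents them as an adverse-event instrument matched to the session log. It also gives set topics and a trained interviewer, not a structured form. True, but the calls will still elicit and record complaints that no one is stated to ask exercisers about.

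Fourth, leg pain is registered at the functional tests (Procedures), which every arm undergoes at baseline and final evaluation with blinded assessors. This is a common source, but it covers two time points and pain at testing, so it cannot replace weekly enquiry.

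A reader might go further and divide session time by clock time: 10 × 2 × 1 = 20 hours of 10 × 7 × 24 = 1,680, or 1.2%, and infer almost no recorded events in the exercise arms. The documents do not support that. The share of hours equals the share of events only if events are spread evenly over time, and exercise-related events are likely to cluster around sessions. Nor do the documents identify delayed musculoskeletal harm as the main safety question.

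**Conclusion.** The point holds in a limited form. As written, harms in the exercise arms are registered when they occur in session, controls are questioned about the whole 10 weeks, and nothing stated closes the gap despite the promise in the Discussion. Exercise-versus-control harm counts would not be comparable, and under-recording of between-session events in the exercise arms is the probable direction, though not a certain one.

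The size cannot be derived from the document. The illustrative risk ratios of 0.10 to 0.50 rest on equal true risk, full capture in controls and an in-session share of 10% to 50%, all assumed. Even at 50%, a true doubling of risk would be recorded as no difference.

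A reader might infer that no harm counts in this trial can be compared, or that the trial's conclusions are biased. Neither follows. The land and aquatic arms share one stated method, so this asymmetry does not affect their comparison. The efficacy outcomes and the sample size do not depend on harms recording. This is a cheap improvement that should be made, not a threat to the trial's main result.

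**What to change.** Ask the questions now listed under Control group once a week in all three arms, with the same wording and the same one-week recall. In the exercise arms, ask them at the first session of the week, or by telephone if the participant is absent. Base any exercise-versus-control harms reporting on this common source only. Keep the session record sheet and report its events separately, labelled as in-session events. Amend Interventions so that it agrees with the Discussion sentence on recording harms.

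The cost is a few minutes per participant per week. Sessions are run in groups of six with at least two researchers present, so no extra visit is needed, only an occasional call for absentees. The sample size, the efficacy analysis and the exercise programmes do not change. Questions asked face to face and by telephone may still draw somewhat different answers, so the mode of each enquiry should be recorded.
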